# Personalized Integrated Care Promoting Quality of Life for Older People: Protocol for a Multicenter Randomized Controlled Trial

**DOI:** 10.2196/47916

**Published:** 2023-07-24

**Keywords:** Parkinson disease, dementia, neurodegenerative, chronic diseases, health care technologies, integrated care

## Abstract

**Background:**

Alzheimer disease (AD) and Parkinson disease (PD) are the 2 most common neurodegenerative diseases affecting millions of people worldwide. The *Personalized Integrated Care Promoting Quality of Life for Older People* (PC4L) project proposes an integrated, scalable, and interactive care ecosystem that can be easily adapted to the needs of several neurodegenerative and chronic diseases, care institutions, and end user requirements.

**Objective:**

The study protocol developed within the framework of the PC4L project aims to iteratively test the integrated platform and its modules, and focuses primarily on assessing the impact of the proposed solution (ie, the PC4L platform) on patients’ quality of life, as well as its usability and feasibility on a large-scale sample size in 3 different scenarios (home, neurorehabilitation, and day care centers).

**Methods:**

A prospective multicenter clinical study is conducted in 5 European countries (Germany, Italy, Portugal, Romania, and Spain) at 6 different pilot centers, for 3 months, in patients with PD, Parkinsonism, AD, and other dementias (ODs). Patients were randomized in a ratio of 1:1 to the intervention group (use of the PC4L system) or the control group (no intervention). The PC4L system consists mainly of a wristband for monitoring parameters such as steps and levels of physical activity, and the PC4L app, which includes different engaging functionalities. Both groups are assessed through baseline and end-of-study clinical evaluations, including assessment of quality of life through the EQ-5D-3L scale.

**Results:**

The study protocol is part of a project approved and funded by the European Commission Horizon 2020 (grant agreement number 875221). The ethics committees of all involved centers reviewed and approved the study protocol. The study began with the recruitment phase in September 2022, and enrollment ended in February 2023. Recruitment is now closed (April 2023). The results of this study are expected to be published in summer 2023. A total of 558 patients, 279 per study group, were recruited. The results will allow to clarify the impact of PC4L on quality of life, will assess the empowerment of patients and the medical resources use, as well as the usability of the final version of the PC4L system. It will also provide information on the support of the system as a tool to facilitate the decision-making process.

**Conclusions:**

The PC4L project intends to test a technology-based, integrated, scalable, and interactive care platform on patients with neurodegenerative diseases and proposes a good coordinated care model between all involved actors. Future developments of the PC4L solution may involve caregivers and socio-health professionals in the decision-making process in order to facilitate efficient communication between all stakeholders and ensure reliable and protected access to data within Europe.

**Trial Registration:**

ClinicalTrials.gov NCT05538455; https://clinicaltrials.gov/study/NCT05538455

**International Registered Report Identifier (IRRID):**

DERR1-10.2196/47916

## Introduction

### Background

There is an urgent need to increase the efficiency and sustainability of health and social care systems across Europe, as there is a growing trend in public spending, which is expected to reach 14% of gross domestic product by 2030 [1]. The aging of the population, accompanied by an increase in chronic diseases, including cardiovascular diseases, diabetes, asthma, mental and physical disorders, and neurodegenerative conditions, represents the main cause of this situation [2,3]. In fact, the existence of comorbidities and the confluence of several chronic diseases are progressively more frequent in older adults, which increases the need to develop models and tools to improve integrated health care systems.

The aging of the population has also led to major reforms in long-term care policy and systems in many European Union (EU) countries, raising the necessity for alternatives. This implies the need for help with household tasks or other practical errands, transport to hospital/clinic visits or social visits, social companionship, emotional guidance, or organizing professional care. In most European countries, much of the care for people older than 60 years is based on informal care [4].

Among the most common chronic diseases in older adults, neurocognitive disorders, such as dementia, Alzheimer disease (AD), and Parkinson disease (PD), are the most disabling. Today, more than 10 million Europeans live with neurocognitive impairment disorders at different stages of dementia.

In recent years in Europe, digitalization is recognized as a powerful tool to achieve many potential benefits such as improving quality of life and putting patients at the center of the care process [5].

Therefore, the current situation can be improved by the creation of an integrated care platform, capable of establishing correlations between comorbidities, investigating the use of polypharmacy, mitigating potential health risks, studying the social variables involved, and promoting unified treatment procedures or social services. This solution could help patients, caregivers, and social health professionals to better monitor several diseases, while also considering the social context [6-8]. Besides, according to a recent work [9], the inclusion of a web platform for monitoring signs and symptoms of older persons by health care professionals over time has proved to be an important resource.

In addition, people with chronic diseases experience difficulties in their daily lives and require specialized care services as well as treatments, imposing high burdens on the public budget: this requires special attention to adequately address the sustainability of the social health system in Europe.

Personalized Integrated Care Promoting Quality of Life for Older People (PC4L) is a European Commission Horizon 2020 project (grant agreement number 875221) that proposes an integrated, scalable, and interactive care ecosystem, and can be easily adapted to the reality of several chronic diseases, care institutions, and end user requirements, benefiting all the involved actors, from patients to caregivers and health professionals. Its main contributions consist of the following:

Building an integrated, scalable, and interactive care ecosystem for neurodegenerative diseases and adaptable to other chronic conditionsFinding the best actions and measures from a medical and social point of view that can facilitate an improved quality of life, awareness, and care management for senior users with neurodegenerative and other chronic diseasesProviding a personalized recommendation and interaction model, which can support the user through gamification techniques, with the final goal of adopting healthy habits, maintaining a good daily routine, and following the prescribed actions by the professionalsEnabling multidisciplinary communication between all involved stakeholders, facilitating better time management for social and health professionals, and contributing to a cost-efficient, flexible, and highly adaptable solution for senior users with short- or long-term conditions

By adopting a user-centered design approach starting from the early stages of the project [10], the inclusion of the needs and requirements of the end users has been crucial toward the PC4L platform development and implementation [11] and the current outline of the protocol presented here. In fact, through the work performed during the first part of the project, we identified the more important factors from the personal, social, and health points of view that are able to influence the daily lives of the end users and reflect on their expectations regarding the PC4L solution.

### Aims

This study represents the third, and last, phase (pilot 3) of large-scale pilots aiming to gradually co-design and iteratively test the PC4L integrated platform and modules.

While pilot phases 1 and 2 focused on technical feasibility and patients’ satisfaction, this protocol focuses on the following objectives:

To assess the impact of using the PC4L platform on patients’ quality of lifeTo compare the metrics generated by the PC4L platform in real-life conditions with the clinical outcome measuresTo evaluate the feasibility and safety of measuring disease progression and patient health status through the global functioning of the PC4L systemTo assess and compare the feasibility and usability of 2 different versions of the PC4L system (fully equipped version vs cloud-based solution)To increase patients’ safety and empowerment

As the primary outcome, the study will provide:

The difference in quality of life between groups (experimental vs control group), measured by the EQ-5D-3L scale at the end of the study

The following secondary outcomes will also be acquired:

The correlation coefficient of the PC4L platform metrics (eg, steps and physical activity levels, sleep, number of falls, cognitive scores) with the clinical outcome measures (eg, motor clinical evaluation, sleep questionnaire, Falls Efficacy Scale-International [FES-I], cognitive evaluations) measured at baseline, end of the study, and the values of change from baselineSystem usability assessment, measured through the System Usability Scale (SUS), at the end of the studyUsers’ satisfaction with the PC4L system, measured through a 5-point Likert Scale, the mHealth User Satisfaction Questionnaire, and the participants’ answers to open questions, at the end of the studyChanges in patients’ satisfaction and empowerment, measured by the Patient Assessment of Chronic Illness Care (PACIC) and the Short Assessment of Patient Satisfaction (SAPS) scales, respectively, at baseline and at the end of the studyChange in patients’ use of medical resources (number of admissions and number of days spent in health institutions) in the last month, measured at baseline and at the end of the study

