#### Metrics

During the monitoring period, specific metrics (Table 1) are collected, continuously and passively, through the PC4L system.

**Table 1 table1:** Metrics and related devices used during patients’ monitoring.

Metrics	Devices
Walking parameters	Wristband and phone
Bradykinesia	Wristband and phone
Loss of balance	Cameras
Falls	Cameras and wristband
Festination	Wristband and phone and camera
Physical activity	Wristband
Freezing	Wristband and phone and camera
Inactivity	Wristband
Compliance with medication	App
Sleeping pattern	Wristband
Interaction patterns with the devices	Platform or app
Usage of the physical activity recommendation services	Number of clicks per week of the different services

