### Study Design

A prospective multicenter clinical study is conducted in 5 European countries: Germany, Italy, Portugal, Romania, and Spain (also including 6 pilot centers).

The pilot sites are (1) Asociacion Parkinson Madrid (APM), Madrid (Spain); (2) Casa di Cura del Policlinico (CCP), Milano (Italy); (3) Campus Neurológico Sénior (CNS), Lisbon (Portugal); (4) University and Emergency Hospital of Bucharest (UHB), Bucharest (Romania); (5) University of Medicine and Pharmacy (UMF), Bucharest (Romania); and (6) Wohlfahrtswerk für Baden-Württemberg (WBW), Stuttgart (Germany).

There are also 3 different scenarios: (1) rehabilitation center (inpatients and outpatients); (2) day care centers; and (3) home set (ie, patients’ home).

The duration per patient, at home and in the day care center, will be up to 3 months. Participants in the rehabilitation center participated during the period of their stay in the center (not exceeding the 3 months).

A specific route diagram is presented in Figure 2 in accordance with the CONSORT (Consolidated Standards of Reporting Trials) guidelines. The protocol of this study was developed in accordance with the SPIRIT (Standard Protocol Items: Recommendations for Interventional Trials) guidelines (Figure 3) [12]. The schedule of enrollment, interventions, and assessments is presented in Figure 3.

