### Recruitment

Patients with PD and other parkinsonian syndromes, AD, or ODs were invited to participate from the clinical centers involved in the study. Each participant organization was assigned to recruit a number of participants related to their skills, experience, number of researchers involved, and access to users (Table 2).

**Table 2 table2:** Distribution of participants per clinical center and scenario.

Scenario/clinical center	Rehabilitation (n=204), n	Day care (n=82), n	Home (n=272), n	Total (N=558), n
APM^a^	80	N/A^b^	26	106
CCP^c^	63	N/A	62	125
CNS^d^	46	N/A	86	132
UHB^e^	15	N/A	15	30
UMF^f^	N/A	30	30	60
WBW^g^	N/A	52	53	105

^a^APM: Asociacion Parkinson Madrid.

^b^N/A: not applicable.

^c^CCP: Casa di Cura del Policlinico.

^d^CNS: Campus Neurológico Sénior.

^e^UHB: University and Emergency Hospital of Bucharest.

^f^UMF: University of Medicine and Pharmacy.

^g^WBW: Wohlfahrtswerk für Baden-Württemberg.

To reach the planned number of recruits, many strategies were implemented: participants were contacted through online webinars; through brochures placed in specific centers such as pharmacies, leisure centers, and medical offices; and through patients’ associations. Further, regular updates were posted via online newsletters on different websites, such as the PC4L website and end users organizations’ websites. In addition, information about the PC4L pilot 3 study was shared during national and international conferences. Recruitment was also promoted in a collaborative way thanks to partners from other European projects. Finally, participants were recruited in person when accessing the medical facilities and via phone contact or emails after searching local databases.

Patients who discontinue the study participation because of medical conditions (ie, infections, falls, medical emergencies) or unwilling to participate any longer for other reasons (ie, difficulty with technology, loss of interest) will be considered dropouts.

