### Study Assessments

In-person assessments took place at baseline and at the end of the study (3 months follow-up or at discharge from the rehabilitation program).

Specifically, the sample characterization and clinical evaluation of the participants (both experimental and control group patients) were performed at baseline. The clinical evaluation with specific tests and scales was repeated at the end of the study.

At the beginning and at the end of the study, all patients were assessed on quality of life through a specific scale (EQ-5D-3L).

Only for patients assigned to the intervention group, their experience with the PC4L platform was assessed in terms of usability at the end of the experimental period.

Figure 3 and the “Data Collection and Analysis” section report specific outcomes that will be used.

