### Statistical Analysis

Descriptive analysis will be performed for all variables to characterize the sample. For continuous variables, mean, SD, median, and range values will be calculated. For categorical variables, absolute and relative frequencies will be used to describe the data [29-31].

Normality will be studied using the Kolmogorov-Smirnov and Shapiro-Wilk tests. The effect of using the PC4L system will be analyzed by applying the paired-sample *t* test (2-tailed) and the Wilcoxon signed rank test to each variable (statistical significance will be set at P<.05).

The Pearson and Spearman correlation tests will be used to validate the PC4L systems metrics (statistical significance will be set at P<.05).

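### The falls metric is named as a count and correlated with clinical scores without any term for observation time, although rehabilitation patients are observed only for their stay and others for up to 3 months

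*Protocol article*

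**What the plan says.** The Aims section names the secondary outcome as "The correlation coefficient of the PC4L platform metrics (eg, steps and physical activity levels, sleep, number of falls, cognitive scores) with the clinical outcome measures", taken at baseline, at the end of the study and as change. Falls appear there as a number, with no denominator and no time window.

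The Metrics section describes collection: "During the monitoring period, specific metrics (Table 1) are collected, continuously and passively, through the PC4L system". Its Table 1 gives the source of the falls metric as "Cameras and wristband".

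Observation time is set in Study Design. For two scenarios, "The duration per patient, at home and in the day care center, will be up to 3 months". For the third, "Participants in the rehabilitation center participated during the period of their stay in the center (not exceeding the 3 months". Study Assessments matches this by placing the final assessment at "3 months follow-up or at discharge from the rehabilitation program". Only a ceiling is given for the rehabilitation stay: no minimum, mean or distribution.

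Table 2 under Recruitment shows how many patients this affects: "Rehabilitation (n=204), n" out of 558.

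The analysis is one sentence under Statistical Analysis: "The Pearson and Spearman correlation tests will be used to validate the PC4L systems metrics", at P<.05. No rate, offset, stratification or adjustment for time is mentioned.

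**The concern.** An event count grows with the time at risk. Two patients with the same underlying fall rate will have different expected counts if one is watched for a 4-week stay and the other for 13 weeks. Neither a Pearson nor a Spearman coefficient can tell that difference from a true difference in falling.

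The consequence depends on the clinical score. If the score is unrelated to time watched, the unequal exposure is noise and the coefficient is attenuated. If the score differs between rehabilitation and the other scenarios, exposure becomes a common cause of count and score, and the coefficient is biased. The direction follows the sign of the scenario difference.

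Comparing platform metrics with clinical measures is the second listed objective, and these correlations are the only validation method the article gives. A distorted coefficient could make a sound falls metric look poor, or lend support to an unsound one.

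**Working it through.** **Figures in the document.** The article states no expected coefficient, fall rate or stay length, so there is no published figure to reproduce for this analysis. Table 2 is consistent: rehabilitation 80 + 63 + 46 + 15 = 204; day care 30 + 52 = 82; home 26 + 62 + 86 + 15 + 30 + 53 = 272; total 558. The rehabilitation share is p = 204/558 = 36.6%. If balanced by arm, about 279 × 0.366 = 102 of the 279 platform users are in rehabilitation and 177 are elsewhere.

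**Assumptions (none in the document).** Rehabilitation stays are uniform on 2-6, 3-8 or 4-13 weeks; everyone else is watched 13 weeks. There are on average 1 or 3 falls per 13 weeks, Poisson given the patient's rate, with a between-patient coefficient of variation of 1. The clinical score has SD 1 within scenario and is shifted by Δ in rehabilitation.

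**Step 1: size of the exposure effect.** At equal fall rates, the ratio of expected counts is 13/4 = 3.25 for stays of 2-6 weeks (mean 4) and 13/8.5 = 1.53 for stays of 4-13 weeks (mean 8.5).

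**Step 2: bias when falls and score are truly unrelated.** With count C, score S and time watched T,

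Cov(C, S) = E[Cov(C, S | T)] + Cov(E[C | T], E[S | T]).

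The first term is zero here. The second is λ · p(1 − p) · (mean stay − 13) · Δ, where λ is falls per week.

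- Stays 2-6 weeks, 3 falls per 13 weeks, Δ = 0.5: covariance = (3/13) × 0.232 × (−9) × 0.5 = −0.241. The mean count is λE[T] = (3/13) × 9.71 = 2.24. The count variance is 2λ²E[T²] − 2.24² + 2.24 = 2 × 0.05325 × 113.55 − 5.02 + 2.24 = 9.31, so its SD is 3.05. The score SD is √(1 + 0.25 × 0.232) = 1.029. Hence r = −0.241/(3.05 × 1.029) = −0.077.
- Stays 4-13 weeks, 1 fall per 13 weeks, Δ = 0.5: the same formula gives −0.040/(1.312 × 1.029) = −0.030.

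Simulation of 300,000 patients under these inputs gives −0.078 and −0.030 for Pearson, and −0.099 and −0.031 for Spearman. With Δ = 0 all are about 0.

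**Step 3: bias when a true association exists.** Simulated with a correlation of 0.3 between log fall rate and score within scenario. Cells are Pearson / Spearman.

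| Stays; falls per 13 weeks | Δ | Raw count | Count per time watched | Equal 13-week window |
|---|---|---|---|---|
| 2-6 weeks; 3 | 0 | 0.18 / 0.18 | 0.20 / 0.19 | 0.22 / 0.22 |
| 2-6 weeks; 3 | +0.5 | 0.10 / 0.08 | 0.19 / 0.16 | 0.21 / 0.21 |
| 2-6 weeks; 3 | −0.5 | 0.26 / 0.27 | 0.19 / 0.22 | 0.21 / 0.21 |
| 4-13 weeks; 1 | 0 | 0.17 / 0.15 | 0.17 / 0.15 | 0.18 / 0.17 |
| 4-13 weeks; 1 | +0.5 | 0.13 / 0.12 | 0.16 / 0.14 | 0.17 / 0.16 |
| 4-13 weeks; 1 | −0.5 | 0.19 / 0.18 | 0.16 / 0.16 | 0.17 / 0.16 |

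Relative to Δ = 0, the raw-count coefficient moves by at most about 0.10 (Spearman 0.179 to 0.077, or to 0.273) and at least about 0.03. Without a scenario difference the loss is modest attenuation. Dividing by time watched removes nearly all of the Pearson shift and most, not all, of the Spearman shift. With 13 weeks for everyone, the three measures agree.

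**Step 4: what this means for the P<.05 rule.** With n = 279, a coefficient of about 1.96/√279 = 0.117 reaches significance. With no true association, the chance of P<.05 is about Φ(|r|√279 − 1.96) + Φ(−|r|√279 − 1.96): 8% at |r| = 0.03, 26% at 0.078 and 38% at 0.099, against a nominal 5%. Using all 279 is an upper limit, since MDS-UPDRS is described for PD and CDRS for the dementias.

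**The case against.** The best reply is that the article never says how falls are summarised. The falls count appears once, in a list of examples beside steps, which also lacks a unit. The phrase about baseline, end of study and change may apply to the platform metrics too, which would suggest windowed values. A condensed article can leave such derivations to the full protocol or analysis plan. Nor does Statistical Analysis say that all scenarios go into one correlation. These points stand: a cumulative total and a pooled correlation are the plain reading, not stated facts. They do not dispose of the point. The article does fix the metric, the tests and an unequal observation period, and as printed these do not fit together. Elsewhere it does set a time basis: service use is clicks per week, and medical resource use refers to the last month.

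A reader might also infer that rehabilitation stays are short, that these patients are clinically worse, and hence that the correlation is systematically wrong whatever the comparator. The documents do not support this. Only the 3-month ceiling is given, rehabilitation includes outpatients, and the Hoehn and Yahr range is the same in every scenario. False positives or a reversed sign need a comparator that differs with time watched.

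Finally, a rate alone is not a complete cure. The fully equipped version, which supplies the cameras, was used only in rehabilitation (70 of 279 users), so detection intensity also differs by scenario.

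**Conclusion.** The point holds in a limited form. As printed, the plan correlates an exposure-dependent count with clinical scores under observation times that differ by design for 36.6% of patients. The certain consequence, if the count is used as it reads and stays are shorter than 3 months, is some attenuation. Bias in either direction follows only where the clinical score also differs by scenario. Its size cannot be known from the document. On the assumed stays, fall rates and a 0.5 SD scenario difference it is about 0.03 to 0.10 on the correlation scale, and it vanishes if everyone is in fact watched for the same time.

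It would go too far to say that the falls validation is shown to be invalid, or that a spurious result is likely. This is one metric of a secondary outcome in the intervention arm. The EQ-5D-3L comparison and the 558-patient sample size are untouched. The change is still worth making, because it costs little and removes an avoidable ambiguity from the validation analysis.

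**What to change.** In Aims and in Statistical Analysis:

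- Define the metric as falls per monitored week, using participation time (or device-worn time, if recorded; the article does not say that it is), or count falls over one common window for all patients.
- Estimate the association within each scenario and then combine, or adjust for scenario. A count model with log monitored time as offset, such as a negative binomial, is an alternative.
- Analyse camera-detected falls separately from wristband-detected falls, since dividing by time does not make the two detection methods comparable.
- Apply the same rule to any other metric that is an event count.

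This changes analysis wording only: no extra patients or visits. The minimum extra input is each patient's start and end of participation. The downside is that rates from short stays are noisy; the offset model handles this better than a correlation of rates, and a common window avoids it at the price of discarding later data.

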#### PC4L Mobile App

The PC4L app includes a prescription dashboard, which monitors drug compliance; questionnaires on health status and physical activity, to be filled periodically; a symptom diary, which registers the symptoms experienced by the patient (ie, falls, freezing, loss of balance); physical activity recommendations; and daily personalized notifications on physical activity, hydration, and nutrition.

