#### Security and Adverse Event Reporting

Any adverse event (serious or nonserious) and any other abnormal clinical, personal, social finding will be recorded in the patient’s case report form. For all adverse events, sufficient information will be pursued to permit the following:

a determination of a temporal relationship;an adequate determination of the outcome of the event (ie, whether the event should be classified as a serious adverse event); andan assessment of the casual relationship between the adverse event and the study requirements.

An abnormal result finding will be classified as an adverse event if 1 or more of the following criteria are met:

the result finding leads to a discontinuation of patient participation in the research study andthe result finding is considered an adverse event by the researcher.

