Regarding the home scenario, the primary advantage of implementing this scenario is the ability to monitor patients at home, measuring their general health condition, asking about their perceived state, and detecting their symptoms (eg, gait disturbances or falls). The acquisition of these data will enrich patients’ perception of their own condition and will allow the comparison between their insight and the clinical and instrumental data. Health professionals, from their perspective, can take advantage of all these data by adapting the prescribed therapy in a highly personalized manner. Thus, patient-doctor communication will be improved, facilitating patients’ engagement with their own health care process.

Central to the study is also the implementation of the PC4L solution in the rehabilitation centers, as such controlled environments involve patients in different kinds of activities, under the supervision of a multidisciplinary team. Here, patients perform personalized treatments in dedicated rooms, such as motor training and exercises connected to ADL, as well as cognitive exercises to improve memory and attention. The main advantages of PC4L in this scenario are (1) the possibility to provide objective information to professionals to study the evolution, treatment personalization, and rehabilitation suggestions; (2) to check the communication between professionals, patients, and caregivers, especially exercise recommendations based on the evolution of patient’s movement skills; and (3) to design a decision support tool taking into account the patient’s personal and health condition.

Finally, in the third scenario of day care centers, patients perform activities connected to ADL like at home, but under the supervision of professionals (day care center workers). Additionally, the participation of caregivers in this scenario can support the patients. The benefits are to check the communication between professionals and the caregiver, who does not live in the same house with the patient, and to monitor the patient’s evolution.

In this pilot study, as already reported by Espay et al [48], low digital skills could be a limitation to the appropriate use of the PC4L solution and, therefore, the correct monitoring of the participants. The consortium mitigated this risk by adopting simplified age-appropriate questionnaires and tools.

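### The only fall-related clinical measure named as a comparator for the platform's metrics is a fear-of-falling score, which cannot validate the fall count

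*Protocol article*

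**What the plan says.** The Aims section lists, as a secondary outcome, the correlation of platform metrics with clinical measures, giving as examples "steps and physical activity levels, sleep, number of falls, cognitive scores) with the clinical outcome measures (eg, motor clinical evaluation, sleep questionnaire, Falls Efficacy Scale-International". The scale named last there is FES-I; cognitive evaluations complete the examples. The Statistical Analysis section gives the purpose: "The Pearson and Spearman correlation tests will be used to validate the PC4L systems metrics (statistical significance will be set at P<.05".

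The Clinical Assessment section describes FES-I as a measure of how afraid patients are of falling, scored from 16 to 64. Nothing else in that battery is a count or history of falls. Its item on events in the last month covers festination, dysphasia, wandering and unplanned use of medical resources, but not falls.

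Falls enter the study in three other places:

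- Table 1 (Metrics) gives the devices behind the platform's fall metric as "Cameras and wristband".
- The PC4L app contains "a symptom diary, which registers the symptoms experienced by the patient (ie, falls, freezing, loss of balance").
- Under Security and Adverse Event Reporting, "Any adverse event (serious or nonserious) and any other abnormal clinical, personal, social finding will be recorded" in the case report form.

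Neither the diary nor the adverse event record is named as a comparator for the sensor count.

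**The concern.** A fall count is a number of events. FES-I is an attitude score. A fearful patient who avoids walking can score high without falling, and a patient with little fear can fall often. If the only fall-related comparator is FES-I, the planned analysis says nothing about whether the falls counted by the sensors took place, or whether falls that took place were counted.

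This matters because the article treats fall detection as a use of the system. The Discussion names, as an advantage of the home scenario, "detecting their symptoms (eg, gait disturbances or falls"), and it links the expected gain in quality of life partly to early detection of signs such as falls. A significant correlation reported as validation would be read as support for those statements, which it could not give.

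**Working it through.** There is no figure in the protocol to reproduce on this point. The check sets the sections side by side, finds the size of correlation that would count as validation, and illustrates what that correlation responds to.

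**1. Sections side by side.** The two example lists in Aims run in the same order: activity and motor evaluation, sleep and sleep questionnaire, falls and FES-I, cognitive scores and cognitive evaluations. FES-I is the only entry in the second list, and the only scale in the Clinical Assessment battery, that is about falling. By the protocol's own description it measures fear.

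**2. Smallest correlation that reaches P<.05.** Inputs: 279 intervention patients, of whom 70 had the fully equipped and 209 the cloud-based version (PC4L System Versions); two-sided 0.05. Formula: r = t / √(n − 2 + t²), with t the 97.5% point on n − 2 degrees of freedom.

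- n = 279: r = 0.117, r² = 0.0138
- n = 209: r = 0.136, r² = 0.0184
- n = 70: r = 0.235, r² = 0.0553

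These assume that every patient supplies both values. With missing data the thresholds rise somewhat.

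**3. What a correlation with fear responds to (illustration only).** None of these inputs comes from the protocol. Assumed: fall propensity and fear correlate at 0.2, 0.4 or 0.6; falls are Poisson with a log-normal rate (log-scale SD 1) and a mean of 0.5 or 2 per patient; 400,000 simulated patients. Spearman correlation of the device count with fear, over those settings:

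- device that counts every fall: 0.10 to 0.43
- device that misses half: 0.08 to 0.36
- device that misses 80%: 0.06 to 0.27
- device that counts each fall five times: identical to the perfect device, because ranks do not change
- device that detects no falls but counts a fear-linked artefact: 0.43 to 0.68

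The last line is high by construction, since its counts were made to depend on fear. It shows only that such a device would not be exposed.

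The approximate chance of reaching P<.05 at n = 279 is Φ(atanh(ρ) × √276 − 1.96). For the device missing 80% of falls, at propensity correlation 0.4 and mean 2, ρ = 0.18 and the chance is about 0.86. For the perfect device at propensity correlation 0.2 and mean 0.5, ρ = 0.097 and the chance is about 0.36. In these examples a poor detector in one population passes more often than a perfect one in another. The result depends heavily on how closely fear and falling are linked, and does not isolate detection quality.

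**The case against.** The strongest reply is that the pairing is inferred. Both lists in Aims are introduced as examples, and no sentence says that the fall count is to be validated against FES-I. The same section writes out a one-to-one match for the PACIC and SAPS scales and does not do so here. Metric-by-metric comparators may stand in a full protocol or analysis plan that is not shown. This stands, and a reader who infers that the protocol expressly fixes the falls–FES-I pair goes further than the text. It does not remove the point: the article says the correlations validate the metrics, and it names no other fall-related clinical measure.

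A second reply is that the stated objective is comparison with clinical measures, so an association with fear of falling is a legitimate result. That is fair for association. It does not fit the word validate.

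A third reply concerns the remedy, and much of it stands. The diary is part of the PC4L app, so it is platform data, although self-reported and not sensor-derived. It is not among the questionnaires that patients were told to complete (Intervention Group). Falls are not named as an adverse event category. No section says that recorded falls carry dates. A reader might infer that data already collected allow falls to be matched by day and sensitivity and false-alarm rates to be computed. The documents do not support that.

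Finally, the simulation rests on assumed inputs. It measures neither the size of the problem in this trial nor the gain from a different reference.

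**Conclusion.** The point holds as a defect in one metric of one secondary outcome. As written, the plan offers only a fear-of-falling score against which to validate the fall count. At n = 279 it would accept a correlation of about 0.117, or 1.4% shared variance, as statistically significant. Such a result shows association with fear and carries no information on missed falls or false alarms.

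This conclusion rests on the protocol's own description of FES-I and on the absence of any other fall-related clinical measure in Aims or Clinical Assessment. It does not depend on the simulation, which is illustrative. The primary EQ-5D-3L comparison and the sample size are untouched.

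**What to change.** In the secondary outcome, name the reference for the fall count. Compare sensor-derived falls in the intervention group with falls recorded in the symptom diary and in the adverse event records of the case report form, at patient level over the monitoring period.

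- Report agreement of the counts, separately by system version, because cameras are not part of the cloud-based version.
- Only where entries are dated, also report the share of recorded falls that the sensors detected and the number of sensor falls with no matching record.
- Keep FES-I as a separate fear-of-falling outcome, and label any correlation with fall counts as exploratory association, not validation.

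The cost is a change of wording and some further analysis of records the study already provides for. The downside is that the reference is imperfect: diary entries are self-reported and may be incomplete, especially in patients with dementia. The result should therefore be described as agreement with recorded falls, not as true detection accuracy.
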